#### Power Analyses

Power analyses were performed before recruitment to estimate the sample size needed based on the HbA1c level as the primary outcome. Given an effect size of 0.35, a significance level of 5%, a standard deviation of the outcome variable of 0.5, statistical power of 80%, and a two-tailed significance test, the sample size was estimated to be 34 individuals in each group. To compensate for dropouts, the sample was set to 50+50 (two intervention groups), and 50 in the control group. A total of 151 patients were included.

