### Statistical Analysis

Baseline measurements will be presented using descriptive statistics. The participants will be block randomized, and the groups should therefore be equal in age and gender distribution. The groups will be compared with regard to clinically relevant variables to ensure they are comparable. Because of the limited size of the groups, they may differ on some variables and, when such variables are identified, they will be adjusted for in the statistical analyses, for example, by treating them as possible confounders.

Baseline data will be compared with data from the normal population (HUNT 3 study) to assess whether our sample is representative of the entire population of Norwegian individuals living with diabetes.

The differences in the main outcome between baseline and 4 months and between baseline and 1 year will be compared between the three groups. First, the crude difference will be analyzed using analysis of variance with post hoc tests (differences between groups). The difference between baseline and the following two measurements within each group will be analyzed using a *t* test. When a change in a selected outcome variable is identified, this change will be modeled using linear regression adjusted for possible confounders.

The cost-effectiveness data will be analyzed using standard statistical analyses depending on the distribution of the data. Missing values will be replaced by imputation. Mean values and 95% CI will be reported for each component of resource use as well as for total costs and effectiveness. Sensitivity analyses will be conducted to handle nonsampling variation.

Our study has a longitudinal design and we expect some dropouts. Therefore, we will perform two analyses: one based on intention to treat and another based on the participants who actually participated actively in our study (per protocol).

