## Results

The inclusion of patients started in March 2011, and 100% of the planned sample size is included (N=151). Of all the participants, 26/151 patients (17.2%) are lost to follow-up by now, and 11/151 patients (7.3%) are still in the trial. Results of the study protocol will be presented in 2014. The aim of this study is to validate and evaluate innovative TM tools on a large scale through a common evaluation, making it easier for decision makers to choose the most efficient and cost-effective technological interventions.

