Research on barriers to intervention has been requested within diabetes self-management interventions [78] and health research in primary care [79]. Barriers to participation and adoption of TM from the perspective of people who decline to participate or who withdrew early from the trial have been described [80]. We do not have permission from the ethical committee to ask patients who drop out during the study for the reasons. In-depth interviews at the end of the study will, however, give us qualitative data about the patients’ views of the intervention’s usability and acceptability. We are also using evaluation tools including questionnaires measuring the same topics [68,69], and we are using the heiQ to identify psychosocial barriers to behavior change [62]. Another concern for some participants is that it is a time-consuming intervention because of its technology focus. Patients may choose not to participate in the study because of the time factor, and this may be a limitation to recruitment. It has been shown that recruitment to primary care trials is normally problematic, such as in the United Kingdom [69]. This may also be a problem in Norway, where there is less research in primary care than in specialist care. However, there is little research on how to improve recruitment in primary care studies. It is important to cooperate with health care personnel in the communities when developing an intervention directed toward “their” patients, and where user involvement is of great importance. Politicians and other stakeholders in the communities should both order and participate in research in this area [7]. This should help increase knowledge and competence for developing new and innovative services for health care users and providers.

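### Intention to treat is the stated answer to dropout, but the HbA1c methods as written use only patients with a follow-up value, so the 1-year result may be complete-case under an ITT label

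*Protocol article*

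**What the plan says.** The Primary Outcome Measure section defines the primary outcome as the between-group difference in change in HbA1c at 4 months and at 1 year. The Statistical Analysis section analyses it by analysis of variance with post hoc tests on the differences from baseline, by within-group *t* tests, and by linear regression of the change adjusted for confounders.

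The same section ends with its response to dropout: "we expect some dropouts. Therefore, we will perform two analyses: one based on intention to treat", the other being per protocol. It does not say how a patient with no follow-up HbA1c enters the first of these.

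The one sentence on missing data, "Missing values will be replaced by imputation", stands inside the cost-effectiveness paragraph. The sentence before it concerns the cost-effectiveness data, and the one after it concerns resource use, total costs and effectiveness.

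The Results section reports that "26/151 patients (17.2%) are lost to follow-up by now", with 11 patients still in the trial. The Discussion adds: "We do not have permission from the ethical committee to ask patients who drop out during the study for the reasons".

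**The concern.** Intention to treat says which patients belong in the analysis and in which group. It does not supply an outcome for a patient who has none. A change score needs both the baseline and the follow-up value, so analysis of variance, a *t* test or a regression run on observed change scores leaves out anyone without the follow-up value. Adding a per-protocol analysis does not help, because it removes further patients.

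Two consequences follow if the text is applied as it stands. The 1-year comparison carries an ITT label but rests on completers. And because each time point is analysed separately, a patient seen at 4 months and lost later contributes nothing at 1 year, although the 4-month HbA1c is the best available guide to the missing value.

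The arms also carry unequal burden. Only the intervention groups use the app for a year, and only one of them has nurse calls, which the Discussion concedes could become tiresome. Differential dropout is therefore plausible. Since patients who leave may not be asked why, the trial will have no stated reasons with which to judge whether the losses relate to outcome.

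**Working it through.** **1. The plan's own sample size.** Inputs from Power Analyses: "Given an effect size of 0.35", "a standard deviation of the outcome variable of 0.5", 5% significance, "statistical power of 80%, and a two-tailed significance test".

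- Normal approximation: n = 2 × (1.960 + 0.842)² × 0.5² / 0.35² = 2 × 7.849 × 0.25 / 0.1225 = 32.04, so 33 per group.
- Two-sample *t* version: 33.02, so 34 per group, which matches the plan.
- Read as a standardised effect, 0.35 would need about 130 per group. It is therefore a raw HbA1c difference, and bias can be compared with it directly.

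**2. Who could be absent at 1 year.** Inputs from Results: 151 randomised, 26 lost, 11 unfinished.

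- Lost so far: 26/151 = 17.2%, leaving 125.
- If all 11 unfinished patients are also lost: (26 + 11)/151 = 37/151 = 24.5%, leaving 114.

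**3. Is power at stake?** The calculation needs 3 × 34 = 102. Both 125 and 114 exceed this. With losses spread equally (an assumption), there are 125/3 = 41.7 or 114/3 = 38 per group, with pairwise power of about 0.89 or 0.86. The step from 34 to 50 per group allows for 1 − 34/50 = 32% loss. Power is not the problem.

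**4. How large could the bias be?** This is an illustration. Apart from the SD of 0.5, the 0.35 target and the 17.2%, its inputs are assumptions, not trial data:

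- no true treatment effect;
- SD of change 0.5 at both times;
- correlation r = 0.6 to 0.8 between 4-month and 12-month change;
- in the app arms, the odds of dropout after 4 months rise by a factor of 2.0 to 4.5 per SD of poorer 4-month change;
- control dropout is unrelated to outcome.

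With m the mean standardised 4-month change among retained app-arm patients (negative means a larger fall in HbA1c), the complete-case 1-year difference is biased by r × 0.5 × m. Control dropout adds nothing under the last assumption.

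| App-arm dropout | Odds ratio | m | Bias, r = 0.6 | Bias, r = 0.8 |
|---|---|---|---|---|
| 17.2% | 2.0 | −0.112 | −0.03 | −0.04 |
| 17.2% | 4.5 | −0.198 | −0.06 | −0.08 |
| 25% | 2.0 | −0.160 | −0.05 | −0.06 |
| 25% | 4.5 | −0.277 | −0.08 | −0.11 |

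Against the 0.35 target, these run from about 10% (0.0335/0.35) to about 32% (0.111/0.35). The 25% rows would go, for example, with 10% control loss, giving (25 + 25 + 10)/3 = 20% overall, between the 17.2% and 24.5% of step 2.

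In this setting dropout depends only on the observed 4-month value, so data are missing at random. An analysis that uses that value brings the bias to about zero; one that ignores it does not.

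**The case against.** The strongest reply is that this is a condensed article and that handling of missing primary-outcome data is commonly left to the full protocol or analysis plan, which are not shown. Nothing in the text says complete-case or observed data only. That would answer a complaint of silence. But the article names the HbA1c methods, offers intention to treat as the consequence of expected dropout, and places imputation under another heading. That combination, followed as written, gives a completers' result.

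Several stronger readings are tempting and are not supported:

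- **That the ITT analysis cannot include dropouts.** Change-score methods can include every randomised patient once values are imputed. The imputation sentence most naturally covers economic data, but it does not expressly exclude HbA1c.
- **That at least 17.2% will be absent.** Lost to follow-up is not stated to mean no 1-year HbA1c. GP journals are a data source (Evaluation Measures, Overview), and usual care includes at least one GP visit a year with HbA1c as a standard measurement. No section says values will be sought after dropout, but none rules it out.
- **That the bias favours the intervention.** Loss by arm is not reported. The Discussion also raises disappointment among patients allocated to control, so uninformative control dropout cannot be presumed.
- **That missingness can never be defended because reasons may not be asked.** Baseline and 4-month data, app logs, support records and nurse notes can still inform a missing-at-random argument.

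**Conclusion.** The point holds in a conditional form. As written, the plan's answer to dropout does not say how patients without a follow-up HbA1c are kept, and its named methods omit them. Unless values are imputed or retrieved from GP journals, between 26 and 37 of 151 randomised patients could be missing from the 1-year primary result, and their 4-month values would be unused.

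The harm is possible bias and a misleading label, not lost power. The direction is unknown from the document. The 0.03–0.11 point range applies only under the stated dropout assumptions; it shows that the effect could be material against a 0.35 target, and it is not an estimate for this trial.

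**What to change.** - **Primary analysis.** Include all randomised patients in their allocated group. Use a linear mixed model for HbA1c at baseline, 4 and 12 months with treatment, time and treatment-by-time terms, keeping baseline in the outcome vector so that patients without follow-up still count. Alternatively, use multiple imputation drawing on baseline and 4-month values. Either replaces analysis of variance of observed change scores.
- **Data.** Use HbA1c from GP journals for patients who drop out, where consent allows.
- **Sensitivity.** Add a delta-adjusted analysis in which app-arm dropouts are taken to be worse by, for example, 0.1 to 0.35 points.
- **Reporting.** Give loss by arm and time point. State whether the imputation sentence covers HbA1c.
- **If none of this is adopted,** call the result complete-case, not intention to treat.

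The cost is a change of wording and modest extra programming, plus record look-up for the GP values. The main analysis would rest on a missing-at-random assumption, which the delta-adjusted analysis is there to test.

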### Ethical Considerations

The study has been approved by the Regional Ethics Committee. The patients will be guaranteed full confidentiality and are required to provide informed consent to participate in the study. The security associated with the server will ensure the safety of the data. Only anonymous data are sent in an encrypted way over the Internet, and the data will be stored anonymously. There are ethical concerns about clinical trials when some of the patients receive the intervention, while others do not. However, all patients will receive the usual care by their GPs, who will be aware of their patients’ participation in the study.

## Results

The inclusion of patients started in March 2011, and 100% of the planned sample size is included (N=151). Of all the participants, 26/151 patients (17.2%) are lost to follow-up by now, and 11/151 patients (7.3%) are still in the trial. Results of the study protocol will be presented in 2014. The aim of this study is to validate and evaluate innovative TM tools on a large scale through a common evaluation, making it easier for decision makers to choose the most efficient and cost-effective technological interventions.

## Discussion

Despite a large number of studies of TM and systematic reviews of the effects of TM, there remains a lack of consensus in research findings [28]. The key elements in this trial are the effect of an intervention that combines a mobile self-management tool with motivational support and the comparison with an intervention comprising TM alone. It is of interest to investigate the effect of the TM application with and without health counseling, and it is reasonable to question whether health counseling is important for the continued use of tools such as those in this study and for patients’ health competence and acceptability. One might question whether the health counseling part of the intervention will motivate the patients or whether the repeated phone calls from the diabetes nurse will become more tiresome than supportive and thus unwanted. Research on this question is needed, but to our knowledge, no studies have investigated this thoroughly.

We have chosen to include adult patients of all ages and some not familiar with mobile phones. Our qualitative approach will allow us to search for possible limitations in the use among different groups of patients. This may give us valuable knowledge about how to encourage the use among different groups of patients and how to assess the effects of a low-intensity intervention on different subgroups. Our qualitative approach might also reveal important information in discussions with patients and health personnel about how to integrate self-management tools in the health care system.

The patients included in the study may represent those who are open to new technology and who are willing to participate in a complex intervention; thus, the acceptability to using such devices may be lower in the wider population. It will be important to assess representativeness. In Norway, we have data from large population-based studies that are well suited for comparison purposes. Recruitment to RCTs is also frequently problematic [73,74], and one concern in the present RCT is whether patients who are eligible will be disappointed when they are randomized to the control group and not to an intervention group receiving the Few Touch application or the application together with health counseling. There is reason to question whether an RCT is suited to this type of study when we are recruiting possibly motivated patients to participate in a TM intervention and they may be randomized to the control group. Different designs that are more flexible and clinically useful have been discussed [73], and our study may contribute to this discussion, which is of current interest.

In the present study, we have chosen HbA1c level as the primary outcome. Many people with diabetes have poor understanding of their HbA1c level, and only few remember their actual test results. The level of agreement between perceived glycemic control and actual HbA1c values is also poor [75]. This could be a challenge in our research when the primary outcome is a measure of which many patients may have a poor awareness and understanding. In addition, glycemic control may not be a goal for some patients when they volunteer for the study. However, the patients in the intervention groups will have access to information about their blood glucose measures through the Few Touch application, and one of the intervention groups will additionally receive health counseling to help them attain self-management and diabetes control.

Evaluations of telehealth interventions for persons with diabetes have focused mostly on the achievement of a clinical outcome in terms of glycemic control. Nolte et al [38] performed an in-depth analysis of outcome measures used to evaluate chronic disease self-management programs and found that decisions about the value and efficacy of chronic disease self-management programs should be interpreted with care. There is an important difference between clinical measures (eg, HbA1c level) and patient-reported outcomes. The former can be assessed relatively accurately, whereas assessments of patient-reported outcomes have considerably more measurement error and varying degrees of bias caused by question interpretation and personal appraisal. There is a need for further research, qualitative studies in particular, to unravel the cognitive processes and the role of response shift bias in the measurement of change [76]. We will take into account this challenge in our study by using several evaluation-based measures requiring a large amount of personal judgment. Our mixed-method design and inclusion of in-depth qualitative interviews of consecutive patients leaving the study will help us identify their experiences and reflections, and will provide a more comprehensive description of the effects of processes in our evaluation of the intervention.

Another concern in a complex intervention such as ours is the benefit of the attention that all the participants receive during the study period from different persons, for example, the effect from the patients’ awareness that they are participants under study (Hawthorne effect) [77]. The intervention groups receive attention from the technical support team during the 1-year use of the tools provided, and all groups may receive attention during the collection of data at the three time points. Finally, the GPs will be aware of “their” patients’ participation in a study in which HbA1c is the primary outcome, and this may induce them to provide better treatment. We must avoid the effects of other possible interventions given by these professionals. The possibility that improvements may be caused by intensified provider consultation has been described in a recently conducted review [28], and researchers should be aware of this problem.

Research on barriers to intervention has been requested within diabetes self-management interventions [78] and health research in primary care [79]. Barriers to participation and adoption of TM from the perspective of people who decline to participate or who withdrew early from the trial have been described [80]. We do not have permission from the ethical committee to ask patients who drop out during the study for the reasons. In-depth interviews at the end of the study will, however, give us qualitative data about the patients’ views of the intervention’s usability and acceptability. We are also using evaluation tools including questionnaires measuring the same topics [68,69], and we are using the heiQ to identify psychosocial barriers to behavior change [62]. Another concern for some participants is that it is a time-consuming intervention because of its technology focus. Patients may choose not to participate in the study because of the time factor, and this may be a limitation to recruitment. It has been shown that recruitment to primary care trials is normally problematic, such as in the United Kingdom [69]. This may also be a problem in Norway, where there is less research in primary care than in specialist care. However, there is little research on how to improve recruitment in primary care studies. It is important to cooperate with health care personnel in the communities when developing an intervention directed toward “their” patients, and where user involvement is of great importance. Politicians and other stakeholders in the communities should both order and participate in research in this area [7]. This should help increase knowledge and competence for developing new and innovative services for health care users and providers.

## Abbreviations

EU: European Union
GP: general practitioner
HbA1c: hemoglobin A1c
heiQ: Health Education Impact Questionnaire
MAST: Model for Assessment of Telemedicine
MI: motivational interviewing
QALY: quality-adjusted life year
RENEWING HEALTH: REgioNs of Europe WorkINg together for HEALTH
SF-36: Short Form-36
SMS: short message service
SUS: System Usability Scale
T2D: type 2 diabetes
TM: telemedicine
